### Inclusion and Exclusion Criteria

Inclusion criteria included adults (aged 18 years or older) currently employed as active duty (ie, not retired or on an extended medical or disability leave) frontline law enforcement officers fluent in English. Exclusion criteria include non-Canadian law enforcement officers, police administrators, civilian employees (ie, nonsworn members), and officers that do not have regular access to a computer with internet access to complete the web-based AMT intervention. Scores on self-reported mental health screening tools completed during the preintervention sessions will be used to match the assignment of participants to experimental or control groups but will not be used to exclude participants based on established cutoff scores for high or severe PTSI symptoms.

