##### AMT Intervention Sessions 3-7 (45-60 Minutes Each)

These sessions will be completed by participants in the experimental group only. The content of each AMT session will be modified from the Lehrer et al [30] HRVBF protocol and informed by practitioner, knowledge user, and stakeholder-informed design workshops to adhere to iKT principles and fit a web-based format [42]. Participants will use the HRVBF app linked via Bluetooth to their HR monitor to engage in paced breathing exercises, view their RSA progress and live HRVBF data, engage with psychoeducational content on the LMS, and complete their homework assignments (ie, paced breathing practice at least twice a day as per protocol) [30]. Participants will also view short video lectures, text, and educational content, and engage in practical exercises during each session. Participants will receive weekly emails with practice reminders and links to useful resources, including links to YouTube videos of their preferred breathing pace. Participants will learn about meta-cognitive and coping skills as they can help mitigate stress in operational, organizational, and personal contexts to foster holistic resilience and well-being.

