Physiological data will be transferred to a 2-time Canada Research Chair in Health Informatics and Big Data expert coinvestigator (CM) via a secure virtual private network (VPN) tunnel and housed on a private cloud-based Big Data analytics platform located within the *Compute Ontario Advanced Research Computing* equipment at the Centre for Advanced Computing (Queen’s University). CM will design the data management, cleaning, and analysis protocols necessary to construct the big data pipeline to process the large amount of continuous data, including matching the time stamps on the physiological data to significant event markers in the AMT intervention (eg, questionnaires, PASAT, and emotional Stroop tasks) and on the HRVBF app (eg, paced breathing exercise). Preprocessed data will then be sent back to the primary research team (JPA, PMD, and SCS) via a secure VPN tunnel and housed on the secure internal University of Toronto server (RES-NAS) for the statistical analyses described below using bespoke syntax and code on various software platforms (eg, Kubios, MatLab, and SPSS). Data from iKT focus groups will be stored in RR’s secure data web-based Al Fresco space and hard copies in her triple-locking filing cabinet in her office at the Memorial University of Newfoundland.

To test the effectiveness of the AMT intervention on reducing PTSI symptoms and improving resilience, we will conduct prepost analyses of the self-reported PTSI (H1) and resilience measures (H2) using separate repeated measures analyses of covariance (ANCOVAs) accounting for demographic covariates for normally distributed data, and ranked repeated measures ANCOVAs for nonnormally distributed data [93]. Variables including sex, gender (H3), age, years of service, and geographic service region (eg, urban or rural; East, Central, or West) will be included as covariates.

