To test the effectiveness of the AMT intervention on improving biological indicators of resilience, prepost analyses of resting HRV parameters (H4), RSA (H5), and recovery from acute stress (H6) will be separately assessed using repeated measures ANCOVAs with sex, gender (H7), age, years of service, and geographic service region as covariates. To determine which factors significantly predict greater changes in biological outcome measures, hierarchical linear regression analyses will be undertaken with self-reported measures and demographic variables entered as predictors in the models. We will also compare weekly changes in HRV and RSA as measured during AMT module exercises with repeated measures ANCOVAs. A main effects analysis of the “time” variable will explore the potential incremental benefit of AMT training and identify at what point during the 6-week intervention significant biological changes occur. Computational approaches to analyzing and visualizing biological indices of resilience will be led by CM, including integration of cardiac (eg, HRV) and respiratory (eg, RSA) rhythms to elucidate patterns of desynchronization before, during, and following AMT.

To explore sex and gender-based contributions to self-report (H3) and objective indices (H7) of PTSI and resilience, the above analyses will include sex and gender as covariates or predictor variables with sex-stratified samples. These findings will clarify any sex-related differences in baseline and postintervention rates of PTSI and resilience among law enforcement officers and whether there are any sex-related differences in the magnitude of treatment effects (H3). Moderated regression analyses will test whether the AMT intervention affects the relationship between sex and PTSI symptoms and resilience. Multiple comparisons will be adjusted with Bonferroni corrections, where applicable.

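### The weekly HRV/RSA time effect, if age and years of service enter as recorded in a standard repeated measures ANCOVA, tests change at age 0 and loses nearly all its power

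*Protocol article*

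**What the plan says.** All of this stands in the protocol article, under Data Security and Analyses unless another section is named.

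- **Weekly analysis.** "We will also compare weekly changes in HRV and RSA as measured during AMT module exercises with repeated measures ANCOVAs". The effect to be read is the main effect of time: that "variable will explore the potential incremental benefit of AMT training and identify at what point during the 6-week intervention significant biological changes occur".
- **Who supplies the data.** Of AMT sessions 3-7 the article says: "These sessions will be completed by participants in the experimental group only". The weekly series therefore has no control arm.
- **Covariates.** For the pre-post physiological outcomes (H4-H6) the model is "repeated measures ANCOVAs with sex, gender (H7), age, years of service, and geographic service region as covariates". The self-report paragraph gives the same list: "Variables including sex, gender (H3), age, years of service, and geographic service region". The weekly sentence gives none of its own.
- **Software.** The work uses "using bespoke syntax and code on various software platforms (eg, Kubios, MatLab, and SPSS"), given as examples.
- **Population.** Eligible officers are "adults (aged 18 years or older) currently employed as active duty" (Inclusion and Exclusion Criteria).

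The article does not say whether numeric covariates are centred, how categorical ones are coded, or whether covariate-by-time terms are in the model.

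**The concern.** Covariates such as age at entry do not vary across the six weeks. In the general linear model form of repeated measures ANCOVA they act on the within-person test only through covariate-by-time terms, which the SPSS repeated measures procedure adds automatically. The line labelled time is then the intercept of a regression of change on the covariates: mean change when every covariate is zero. In a sample aged 18 or older that is an extrapolation far outside the data.

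In a two-arm analysis this matters little, because the reader looks at arm by time. Here only the AMT arm is measured weekly, so the time effect is the whole omnibus test. A clear average gain could come out non-significant and be reported as no incremental benefit. If change depends on age or service, the test could also be significant when the average change is nil.

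**Working it through.** **Inputs from the article.** Recruitment gives a minimum of 128 and a target of about 250, half in AMT, so the AMT arm has 128/2 = 64 or 250/2 = 125 officers. Six weekly occasions follow from the six-week intervention. The 128 can be reproduced as a two-group comparison on a single measurement: f²N = 0.0625 × 128 = 8, F with 1 and 126 df, power 0.80. It says nothing about the weekly test and is used here only for arm size.

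**Assumptions (not in the article).** Age mean 40, SD 8. Years of service equal age minus 27 plus independent variation with SD 4. Outcome SD 1, equal within-person correlation 0.6, linear gain g over the six weeks in SD units. Only age and service are modelled.

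**Step 1, what the time effect is.** For each within-person contrast, d = a + b₁·age + b₂·service + error. The time test is of a. Relative to centred covariates, its variance is multiplied by V = 1 + m′S⁻¹m, where m and S are the covariate means and covariance matrix.

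**Step 2, size of V.** Age and (service − age) are uncorrelated here, so V = 1 + (40/8)² + (27/4)² = 1 + 25 + 45.56 = 71.56. The standard error is 8.5 times larger. Age alone gives V = 26.

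**Step 3, power.** For a linear gain over six occasions the squared deviations sum to 0.7g². Centred, λ = n × 0.7g²/(1 − 0.6) = 1.75ng². Uncentred, λ is divided by V. The test is F with 5 and 5(n − 3) df.

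| n | g | λ centred | Power centred | λ uncentred | Power uncentred |
|---|---|---|---|---|---|
| 64 | 0.3 | 10.08 | 67% | 0.14 | 6% |
| 64 | 0.5 | 28.00 | 99% | 0.39 | 7% |
| 125 | 0.3 | 19.69 | 95% | 0.28 | 6% |
| 125 | 0.5 | 54.69 | >99% | 0.76 | 9% |

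Simulation with the same inputs (4,000 runs per row) gave 67%, 99%, 94% and 100% centred against 5%, 7%, 5% and 8% uncentred.

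**Step 4, sensitivity.** With age mean 38, SD 8, service mean 12, SD 7.5 and age-service correlation 0.85, V = 45.0 and uncentred power over the same four rows is about 6-11%. With correlation 0.70, V = 29.4 and it is about 6-15%. The loss is severe in each case.

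**Step 5, false change.** If nobody changes, λ = 0 and both versions hold about 5% (simulated 5.3% and 5.0% uncentred). Now let average change be zero but let it vary by 0.2 SD per SD of age, that is 0.2/8 = 0.025 SD per year. At age 0 the fitted change is −40 × 0.025 = −1.0 SD.

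- n = 64: λ = 1.75 × 64 × 1.0²/71.56 = 1.57, rejection 13%.
- n = 125: λ = 3.06, rejection 22%.

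At 0.3 SD per SD of age the fitted change is −1.5 SD, λ is 3.52 and 6.88, and rejection is 25% and 49%. Separate simulations of this setting ranged over 12-27% at 64 and 22-51% at 125. The centred test rejects 5-6%. The smaller V in Step 4 gives higher false-change rates, since the extrapolated change is then estimated more precisely.

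**Step 6, what is untouched.** Adding an arm term gives d = a + c·arm + b₁·age + b₂·service. Moving the origin of age changes a but not c, unless arm-by-covariate terms are added. A week-by-week contrast evaluated at average covariates is a + b₁·(mean age) + b₂·(mean service), which is the same however age is coded.

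**The case against.** The strongest reply is that the article never makes this error in words. It does not say that age and service enter uncentred. The covariate list belongs to the pre-post sentence, not the weekly one. Covariate-by-time terms are not specified, SPSS is only one of three examples, and a model with covariates as main effects only would escape the problem. Centring is a detail that a condensed article may leave to the analysis plan. The weekly analysis is also described as exploratory, and no comparison between arms depends on it.

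Most of this stands and sets the limits of the point, which is conditional. It does not dispose of it. An ANCOVA needs covariates and the article offers only one list. The article also goes beyond silence on a detail: it fixes both the method and the effect to be read, and that pair fails under a standard default unless an unstated condition is met.

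Three stronger readings are tempting, and the document does not support them.

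- *The pre-post efficacy results for H1, H2 and H4-H6 are compromised.* The article names a time main effect only for the weekly analysis, and the arm-by-time term is unaffected.
- *The test generally declares false change.* It holds its level when nobody changes. The inflation needs change that varies with age or service, and the article gives no such slope.
- *The conclusion on when change occurs must be wrong.* Timing needs week-by-week comparisons. If these use means adjusted to average covariates, coding does not alter them.

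**Conclusion.** The point holds for the omnibus time test in the weekly AMT-arm analysis, and only if age and years of service enter as recorded in a model with covariate-by-time terms. Under that reading the test has almost no power whatever the true average gain within the range examined: 5-9% in place of about 65-100% under the main assumptions, and no more than about 15% under the alternatives tried. False positives arise only where change varies with age or service. The age and service distributions, the within-person correlation, sphericity and the linear gain are all assumptions; the article gives none of them. Since the analysis is exploratory and no arm comparison depends on it, this should be corrected but does not threaten the trial's efficacy tests.

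**What to change.** In Data Security and Analyses, add one sentence to the weekly time analysis that adopts one of two routes:

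1. Mean-centre age and years of service, and effect-code sex, gender and region, before the time effect is tested. Plain effect coding weights categories equally, so where categories are very unequal, use the weighted form (mean-centred indicators) to keep the reference at the sample average.
2. Take the time effect from a model with week as a factor, the covariates as main effects, and no covariate-by-time terms.

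Under either route, report mean change by week at sample-average covariates with 95% confidence intervals. This needs a line of code and no new data. Centring leaves fitted values and the arm-by-time tests unchanged, so it has no downside.

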### Biological Resilience Training: Heart Rate Variability Biofeedback

Research reveals a connection between respiration, arousal, and emotional control, such that how a person breathes sends signals to regions in the brainstem and forebrain that modulate arousal [28]. For example, periods of slow breathing are associated with SNS suppression and PNS stimulation, which may underlie the anxiety- and stress-reducing effects of RSA [28]. For nearly 3 decades, Lehrer and Gevirtz [21] have pioneered and refined a cardiorespiratory intervention called heart rate variability biofeedback (HRVBF). During HRVBF, a person is shown visual feedback of their beat-by-beat HR data while engaging in slow breathing with the goal of maximizing RSA. For clinically effective treatment, it is not sufficient to simply instruct a person to breathe slowly. Rather, HRVBF technology is required to identify the precise breathing rate for maximizing individual RSA and to condition this rate through training [29,30].

In collaboration with expert police practitioners as well as medical and academic experts in psychophysiological risk and resilience, the lead author developed the International Performance Resilience and Efficiency Program (iPREP), an in-person resilience program that improves occupational health and performance by addressing the unique acute and chronic stressors faced by police [31-33]. This program has been refined across 6 grant-funded multimethod studies with over 300 police participants measuring objective psychophysiological and behavioral data [31-40]. The components of the currently proposed intervention are based upon the same core scientific principles and validated intervention methods as iPREP, including mental health awareness and support [2] and psychophysiological techniques (ie, HRVBF) to promote resilience by conditioning adaptive HRV, RSA, and HR functioning [30,41,42]. Research has shown that the autonomic modulation techniques instructed during iPREP result in significant, long-term reductions in occupational errors and improvements in officers’ ability to recover quickly from acutely stressful events when completed during scenario-based, in-person training [31-33].

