##### Session 2: Baseline Physiological Assessment and Introduction to AMT (40-60 Minutes)

All participants will be taught via web-based video modules how to apply the wearable HR monitor and configure the HRVBF app. The wearable HR monitor will automatically record date and time-stamped physiological data upon contact with the skin via the chest band and will communicate with the HRVBF app via Bluetooth. All HRV data will be stored locally on the HRVBF app and study device, which will be mailed back to the research team at the end of the study period. In the first part of this session, both experimental and control participants will provide baseline resting HRV and RSA data that will be recorded while participants engage in a 7-minute neutral activity (eg, listening to prerecorded sounds) that does not stimulate arousal or relaxation ([name], unpublished data, 2019). To assess recovery from an acute stressor, participants will perform web-based versions of the Paced Auditory Serial Addition Test (PASAT) [87] and the emotional Stroop task [88], both of which have been shown to induce significant sympathetic arousal but do not simulate traumatic material [28].

Following these baseline physiological assessments, participants in the experimental group will continue with the rest of their session (15-20 min) and begin the AMT intervention. Participants in the control group will not have any programming until session 8 (postintervention assessment).

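### The weekly HRV and RSA series is an uncontrolled training curve and cannot date a change in resting autonomic function

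*Protocol article*

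**What the plan says.** Data Security and Analyses fixes three things for the weekly analysis.

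- The data: "We will also compare weekly changes in HRV and RSA as measured during AMT module exercises with repeated measures ANCOVAs".
- The test: "A main effects analysis of the “time” variable will explore the potential incremental benefit of AMT training".
- The conclusion: to "identify at what point during the 6-week intervention significant biological changes occur".

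On sessions 3 to 7 the article says: "These sessions will be completed by participants in the experimental group only". In them participants "engage in paced breathing exercises, view their RSA progress and live HRVBF data". The background section on heart rate variability biofeedback describes the technique as "engaging in slow breathing with the goal of maximizing RSA", and adds that "HRVBF technology is required to identify the precise breathing rate for maximizing individual RSA and to condition this rate through training".

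Controls take part in the first part of session 2 and in session 8, with nothing scheduled between. The 7-minute neutral task, which gives resting HRV, is described only at those two sessions, in both arms.

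**The concern.** The analysis is meant to put a date on biological change, but its measurements are taken while participants perform an exercise designed to move those same measurements. The exercise is trained and practised at home, so performance should improve with time whether or not anything changes at rest. No untrained group is measured weekly, so nothing can be subtracted.

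At stake is a secondary statement that reads easily as a finding about how long AMT takes to work. Someone planning a shorter or longer programme could rely on a week of onset that reflects practice.

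**Working it through.** **1. Where the measurements exist**

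| Measurement | AMT arm | Control arm |
|---|---|---|
| Neutral-task HRV, session 2 | yes | yes |
| HRV and RSA during exercises, training weeks | yes | none |
| Neutral-task HRV, session 8 | yes | yes |

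Controls may take sessions 3 to 7 after their session 8. That could add training data, but not a concurrent untrained series.

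**2. What a weekly contrast contains**

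Write the mean in week *w* as R(w) + A(w) + L(w) + C(w): resting level, acute effect of the exercise, learning, and calendar trend. The contrast of week *w* with week 1 estimates ΔR + ΔA + ΔL + ΔC. With one arm and one recording condition, only this sum can be estimated.

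If the exercise is the same each week, A is constant and ΔA = 0. The acute effect then cancels, but ΔL and ΔC do not.

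**3. How small a change is called significant**

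The plan gives no figure for this analysis. Its one design figure, a minimum total of 128, is reproduced by a two-group F test with f = 0.25 (power 0.801). It is not in dispute and serves here only to set a lower arm size.

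- AMT arm: 250/2 = 125 as planned; 128/2 = 64 at the minimum.
- Unadjusted 5% threshold, in SDs of the within-person change: 1.96/√125 = 0.175.
- With Bonferroni over five contrasts against week 1 (an assumption; the article applies Bonferroni where applicable): 2.576/√125 = 0.230, and 2.576/√64 = 0.322.

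These are detection thresholds. They do not estimate bias.

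**4. Illustration with no resting change**

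Assumed values, none from the article: six weekly measurements in one arm, within-person correlation 0.7, true resting change zero, and learning equal to T × (1 − exp(−(w − 1)/2)) in units of the between-person SD. There were 1,500 runs per setting.

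| Learning plateau T | Time effect significant, n = 125 | n = 64 |
|---|---|---|
| 0 | 5% | 5% |
| 0.2 SD | 69% | 39% |
| 0.3 SD | 97% | 74% |
| 0.5 SD | 100% | 99.7% |

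The named week also moves with sample size. At T = 0.5, week 2 is the first significant week in 57% of runs with n = 125 and in 27% with n = 64. Hand check:

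- Week 2 gain: 0.5 × (1 − e^−0.5) = 0.197 SD.
- SD of the change: √(2 × 0.3) = 0.775.
- Ratio: 0.197/0.775 = 0.254, above the 0.230 threshold for 125 and below the 0.322 threshold for 64.

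**5. If the series started from the session 2 resting value**

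A constant exercise effect of 0.3 SD would by itself make the first step significant (unadjusted 5%) in 99% of runs (n = 125) or 85% (n = 64). The article does not say the series is anchored this way.

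**The case against.** Four points can be made for the plan.

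- The analysis is presented as exploratory and carries no numbered hypothesis. H4 to H6 rest on separate pre-post analyses with both arms measured. This stands, and it limits the point to a secondary claim.
- The text speaks of biological changes, not resting ones. RSA under paced breathing is listed among the session 8 measures, and the introduction treats a rise in RSA as building capacity. So the in-exercise series is not merely a skill score. This stands too, but it does not make the series controlled or separate practice from lasting change.
- A constant acute effect cancels between training weeks, and with no learning the test holds its 5% level. Correct. The problem lies in what varies with time.
- A condensed article may leave exercise content and standardisation to the full protocol. Also fair. Standardising the exercises would deal with content, but not with learning or calendar trend.

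A reader might infer that the time effect reflects only the exercise and no biological change. The documents do not support that: the two cannot be distinguished, and either may be present. A reader might also infer that breathing pace or content changes weekly. The article says a rate is identified and conditioned, but gives no session-by-session schedule. Nor does anything here undermine the main efficacy tests.

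**Conclusion.** The point holds in limited form. As specified, the weekly time effect describes how HRV and RSA during AMT exercises develop in trained participants. It cannot show when resting autonomic function changes, because skill, any differences in exercises and calendar trend produce the same pattern and no concurrent comparator exists.

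The size of any distortion cannot be derived from the article. The simulation shows that modest learning would be enough to produce a significant time effect and a named week. Its percentages depend on the assumed correlation, learning curve and contrasts. The consequence is confined to the timing statement.

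**What to change.** **Wording, at no cost.** Describe the in-exercise series as an uncontrolled training curve within the AMT arm. Remove the claim that it identifies when biological change occurs. State that the only controlled comparison is session 2 to session 8.

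**If the timing of resting change is still wanted.** Record the existing 7-minute neutral task in sessions 3 to 7 before any paced breathing. Run the weekly analysis on those values together with the neutral-task values from sessions 2 and 8. Keep the uncontrolled label, since controls would still have no weekly data.

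The monitor, app and task are already in place. The burden is about 7 minutes on a session of 45 to 60 minutes (7/60 = 12% to 7/45 = 16%), plus possible effects of repeated testing, in a study already allowing for attrition. If that is too much, the wording change alone is sufficient.

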**Methods:**

The study is comprised of 2 phases. Phase 1 involves the development of the web-based AMT intervention, which includes 1 session of baseline survey measures, 6 weekly sessions that integrate HRV biofeedback (HRVBF) training with meta-cognitive skill practice, and 1 session of follow-up survey measures. Phase 2 will use a cluster randomized control design to test the effectiveness of AMT on the following prepost outcomes: (1) self-report symptoms of PTSI and other wellness measures; (2) physiological indicators of health and resilience including resting HR, HRV, and RSA; and (3) the influence of sex and gender on other outcomes. Participants will be recruited for an 8-week study across Canada in rolling cohorts.

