### Recruitment

We aim to test the AMT intervention on a sample of approximately 250 frontline police officers in rolling cohorts of 10-15 participants (half AMT, half waitlist control) from geographically representative police services across Canada. A power analysis was conducted using G*Power software [43] and found that a minimum total sample size of 128 participants was required (effect size f=0.25, α=.05, power=0.80, number of groups=2, number of repeated measures=2). However, we plan to oversample officers by sex and mitigate possible attrition based on the principal investigator’s previous experience with conducting longitudinal research on police officers [31-33]. A small laboratory-based prepilot sample (n=10) will test equipment reliability, accuracy, and integration of HR monitors with HRVBF and learning management system (LMS) platforms. An initial pilot cohort 1 (n=30) will then test the AMT intervention in the population of interest (ie, law enforcement officers) using a combined laboratory-remote paradigm to validate the implementation of study procedures. These participants will also be invited to participate in a poststudy focus group as per the study protocol (see iKT Focus Groups in Procedures) to optimize the intervention (ie, content and delivery) and overall study procedures to provide stakeholder- and user-informed feedback. When all user feedback has been incorporated, all subsequent participants will be tested fully remotely and in accordance with the randomized control trial procedures and group allocation.

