##### Session 8: Postintervention Assessment (2 Hours)

All participants will receive an email reminder 1 week before the final session, which will be completed by both experimental and control participants. It will begin by obtaining objective physiological measures at rest, including HRV (7-minute neutral task), RSA (paced breathing), and recovery from acute stress (PASAT and Stroop tasks). Next, participants will complete the same self-reported questionnaires as in session 1 to assess changes in self-reported PTSI, resilience and well-being, occupational and operational stress exposure, and sex and gender-relevant data (see hypotheses). Participants in the control group will be asked if they would like to complete the AMT intervention. If so, they will be provided access to sessions 3 to 7 and will be asked to complete a second postintervention assessment (session 8) after completing the AMT intervention. Incentive payments will be processed as participants drop out or complete study assessments.

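### The weekly HRV and RSA analysis names repeated measures ANCOVA, which as classically run uses only officers with all six sessions; a mixed model would use every recorded session

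*Protocol article*

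**What the plan says.** The Methods part of the abstract describes the intervention as "6 weekly sessions that integrate HRV biofeedback (HRVBF) training with meta-cognitive skill practice". The session descriptions agree: AMT begins in the second part of session 2 and continues through sessions 3 to 7, which makes six. Of sessions 3 to 7 the article says "These sessions will be completed by participants in the experimental group only", and controls have no programming between the baseline recording and session 8. Weekly values therefore exist in the AMT arm only.

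For these values, Data Security and Analyses names the method: "We will also compare weekly changes in HRV and RSA as measured during AMT module exercises with repeated measures ANCOVAs". It adds that a main effect of time will explore incremental benefit and "identify at what point during the 6-week intervention significant biological changes occur". The same section gives Kubios, MatLab and SPSS as examples of software.

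Incomplete follow-up is foreseen. Recruitment plans a larger sample partly to offset possible attrition, and the session 8 description says "Incentive payments will be processed as participants drop out or complete study assessments". The article gives no dropout rate and no missed-session rate. For a missed session it states neither a complete-case rule nor imputation nor a mixed model.

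**The concern.** Classical repeated measures ANCOVA works on each person's full set of time points. At the default in SPSS, a person with one missing level is removed from the whole analysis. With two time points, as in the prepost tests, this costs only those lacking one of the two. With six the loss compounds: an officer who skips one week, or stops after session 5, contributes nothing, even for weeks that were recorded.

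The design makes some gaps likely. After the pilot cohort, officers take part fully remotely, fit the chest band themselves, rely on a Bluetooth link, and return the device holding the data by mail.

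At stake is the precision with which the analysis can place the start of biological change. If missing sessions are related to how an officer responds, the shape of the curve is at stake too.

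**Working it through.** **The plan's own figure.** The article states no sample size for the weekly analysis. Its one power calculation (Recruitment) gives a minimum of 128 with "effect size f=0.25, α=.05, power=0.80, number of groups=2, number of repeated measures=2". As a two-group F test this reproduces: noncentrality f²N = 0.25² × 128 = 8, with 1 and 126 degrees of freedom, gives power 0.801. It rests on two measurements and says nothing about a six-session analysis.

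**Inputs.**
- Sessions: 6 (abstract, Methods; session descriptions).
- AMT officers: 250/2 = 125. Recruitment gives about 250 officers in cohorts split half and half. Using all 250 is an assumption, because a pilot cohort of 30 precedes the fully remote randomised phase; without it the figure is (250 − 30)/2 = 110. The percentages below do not depend on this number.
- Chance p of missing any one session: not in the article. Assumed 5%, 10% and 20%, independent across sessions.

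**Formulas.** Share with all six sessions = (1 − p)^6. Recorded sessions = 750 × (1 − p), where 750 = 125 × 6. Sessions used under complete-case analysis = 750 × (1 − p)^6. Share of recorded sessions unused = 1 − (1 − p)^5.

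| p | All six | Officers of 125 | Recorded | Used | Unused |
|---|---|---|---|---|---|
| 5% | 73.5% | 92 | 713 | 551 | 23% |
| 10% | 53.1% | 66 | 675 | 399 | 41% |
| 20% | 26.2% | 33 | 600 | 197 | 67% |

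If only sessions 3 to 7 enter (exponent 5), about 97, 74 or 41 officers are complete, and 19%, 34% or 59% of recorded sessions go unused.

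**Pure dropout.** Suppose the same share p of sessions is missing, but only because officers stop, with stopping equally likely after session 1, 2, 3, 4 or 5. A dropout then misses (5 + 4 + 3 + 2 + 1)/5 = 3 sessions on average, so a share 6p/3 = 2p of officers drops out and 1 − 2p is complete. At p = 10%, that is 100 complete officers, 600 of 675 recorded sessions used, and 75/675 = 11% unused. At 5% and 20% the unused share is 5% and 25%. The pattern of gaps therefore matters as much as their rate.

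**Precision.** With independent misses, a contrast of one session against another could use 125 × (1 − p)² officers, but complete cases give 125 × (1 − p)^6. The standard error from complete cases is larger by the factor √[(1 − p)²/(1 − p)^6] = (1 − p)^−2, which is 1.11, 1.23 or 1.56. At 10%, this compares about 101 officers with 66.

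**Bias.** An illustrative simulation assumed a true mean gain of 0.50 over six sessions, a first session that is always recorded, and a 10% base miss rate. Completers showed a gain of 0.50 when misses were unrelated to response, and 0.57 to 0.63 when officers with smaller gains missed more sessions.

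**The case against.** The strongest reply is that the article never says incomplete officers are dropped. A reader might infer that the result will come from full completers only, but that rests on the usual behaviour of the method, not on the text. The software is listed only as examples, and imputation before the ANCOVA would avoid the loss. How a missed session is handled is also something an article may leave to an analysis plan. This stands, so the absence of a missing-data rule is not the point here. What remains is that the article does name a model, for six self-administered sessions, and that a better-suited one is available at almost no cost.

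A reader might also infer that the curve must be biased, or that officers who stop early are the ones who carry the answer. Neither is supported. Bias needs missingness related to response, which nothing in the article shows. Early stoppers have no later values; they add information on the early weeks, while completers inform all of them.

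The size is assumed throughout. Independent misses are an unfavourable pattern for complete-case loss, and the dropout calculation gives much less. The article also has measures against gaps: a second consent after session 1 and weekly email reminders.

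Finally, the analysis is worded as exploratory, belongs to no numbered hypothesis and has no control data. That also stands and limits the importance of the point.

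**Conclusion.** The point holds in a limited form. The method named for the weekly analysis would, as classically run, set aside recorded sessions from any officer with a gap unless the values were imputed. With 125 AMT officers and independent misses of 5% to 20% per session, complete records fall to between 92 and 33 officers, and 23% to 67% of recorded sessions go unused; under pure dropout with the same share missing, 5% to 25%. The rates, the patterns and the 125 are assumptions. Loss of precision follows whenever sessions are missed; distortion of the curve is conditional on missingness being related to response.

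It would be wrong to read this as a threat to the trial's efficacy results. H1 to H6 are tested by separate prepost analyses, which this point does not touch. Severity is modest.

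**What to change.** Replace the weekly repeated measures ANCOVA with a linear mixed model: session as a categorical fixed effect, a within-person correlation structure, the covariates already listed for the biological outcomes, and all recorded sessions from every officer who started AMT. State that it is valid if data are missing at random; it does not remove bias when missingness depends on unrecorded values. As a check, show the curve by last session reached. Report the result as exploratory change within the AMT arm.

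The cost is a sentence or two in the plan and a small amount of analysis work. No new data, visits or participants are needed.
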